### Dissemination policy

We will do effort to disseminate the study findings through publications in peer-reviewed journals and conference presentations.

## Discussion

Blinding is usually not feasible in RCTs involving healthcare techniques that require manual manipulation [23], including HSM. Consequently, patients will clearly know whether they are receiving the experimental intervention, and patient preference may cause uncertain effects on the study process and results [24, 25]. To reduce patient preference effects, we chose to perform a randomized patient preference trial, from which several advantages can be derived. First, this design allows us to analyze patient-preference effects by comparing the results of compulsory and voluntary randomization. Another benefit of a compulsory randomization group is avoiding being unable to achieve randomization when the proportion of patients who choose voluntary randomization is too small. Second, evaluation of randomized and nonrandomized samples will improve the reliability of the results if they can be corroborated. The evidence from nonrandom samples will also have better external validity. Third, this design will allow the study to recruit more participants, and the patients in the patient preference cluster will be more adherent to the protocol and less likely to be lost to follow-up.

A potential limitation of this study is that the patients in the HSM group may not easily adhere to the 6-month HSM treatment regimen, especially when the weather is hot. Although we will provide air-conditioned rooms at each study site for them to administer HSM, there is no guarantee that all patients will be willing to visit during the hot months of the summer. Nevertheless, patient compliance is an important outcome, and poor compliance would suggest that this community-based HSM model is not feasible. In addition, although the hypertensive symptom scale implemented in this study is from an authoritative guideline and has been used in a number of studies [15] to date, there is no direct evidence to support its reliability and validity.

In summary, this will be the first RCT to evaluate the efficacy, safety, economics, and compliance profile of community-based HSM for primary hypertension and will produce nonrandomized evidence. The study will have a sufficient sample size to obtain accurate estimates, as well as sufficient 6-month follow-up data to verify long-term safety and patient compliance. If proven to be a safe and cost-effective method, HSM is expected to be widely promoted in primary healthcare for the treatment of primary hypertension in low- and middle-income countries. Such efforts may also promote the development of relevant industries, such as mugwort cultivation and moxibustion material production.

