### Interventions and cointerventions

In the HSM group, patients will self-administer HSM to treat hypertension. At trial entry, physicians will follow a predetermined standard operating procedure to stimulate the patient for heat-sensitized sensations using round-trip meridian, circling, and sparrow-pecking techniques around any of the acupoints at Yongquan (KI1), Shenque (CV8), and Baihui (GV20) as well as Dazhui (GV14), Quchi (LI11), Hegu (LI4), Taichong (LR3), and Zusanli (ST36). The former three are the main acupoints, and the latter four are the matching acupoints. The patients will select one main acupoint and one matching acupoint with the strongest heat-sensitized sensation as acupoints for HSM self-administration. For bilateral matching acupoints (i.e., Quchi, Zusanli, Hegu, and Taichong), the side with the stronger heat-sensitized sensation will be selected. The administration of HSM at the matching acupoint can be abandoned if all fail to stimulate heat-sensitized sensations.

After acupoint selection, the physicians will explain in detail the technique of HSM to the patients or their families, including how to use the moxibustion jar, ignition, and safety precautions (e.g., preventing burns and smoke evacuation). When dose saturation is achieved (i.e., the heat-sensitized sensations disappear), HSM can be stopped, or the patient can wait until the moxa column has burned completely (approximately 30 min). We will recommend that patients administer HSM once per day at home or at a community healthcare center. Driven by the pragmatic design, we will allow for a lower frequency of HSM when patients are busy, but the procedure must be completed at least two times per week.

Patients in both the HSM and control groups will maintain the use of their original antihypertensive regimen, including antihypertensive drugs or no treatment. The study treatments will last 6 months for all patients. During the trial period, all patients will be prohibited from receiving other acupoint stimulation therapies, such as acupuncture, acupressure, transcutaneous electrical stimulation, or acupoint application therapy. Regular treatment for comorbidities, such as glucose-lowering drugs for patients with diabetes and lipid-lowering drugs for those with dyslipidemia, will be allowed.

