#### Secondary outcomes

A change in mean DBP (mmHg) at month 6 as measured with SBP.The response to treatment at month 6, which is defined as an SBP reduction of ≥ 20 mmHg or DBP reduction of ≥ 10 mmHg for all patients, achieving SBP < 140 mmHg and DBP < 90 mmHg for patients ≥ 65 years or SBP < 130 mmHg and DBP < 80 mmHg for patients < 65 years [17].A change in the mean dosage of the original antihypertensive drug at month 6. At each visit, the physician will decide whether to adjust the original antihypertensive regimen administered to control blood pressure within the ideal range according to the blood pressure measurement, which will be recorded to assess this outcome.A change in mean QoL at month 6, as assessed by the Euro-QoL-5 Dimensions-5 Levels (EQ-5D-5L) questionnaire [19]. This questionnaire includes five items that evaluate QoL in terms of mobility, self-care, usual activities, pain/discomfort, and anxiety/depression. Each item receives a score from 1 to 5 (1, optimal QoL; 5, extremely poor QoL), and a comprehensive index value is calculated from these items, ranging from 0 (extremely poor QoL) to 1 (optimal QoL). The questionnaire also has an overall health status item assessed by a visual analog scale and scored between 0 and 100. A higher score indicates a better overall health status.A change in the mean severity of hypertensive symptoms scored by the symptom scale in the Guiding Principles of Clinical Research on New Drugs of Chinese Medicines at month 6 [20]. The scale assesses 24 hypertension-related symptoms. Each item receives a score of 0 to 3, and a higher score indicates higher severity of that symptom; the total score is the sum of the individual item scores and ranges from 0 to 72 (see details in Additional file 1).Incidence of new-onset cardiovascular events at month 6, including angina, myocardial infarction, and stroke. These data will be collected from patients and family self-reports.Patient compliance with HSM at each visit. This will be determined by the dosage of each administration and the weekly frequency of applications.Cost-effectiveness at month 6, as calculated by comparing the ratio of total treatment cost (China Yuan) to the rate of patients who achieve the targeted response to treatment between the HSM and control groups. Total and antihypertensive treatment costs will be analyzed. Outpatient and inpatient treatment frequencies and costs will also be compared.

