### Visit schedule

Patients will attend a baseline visit and 6 monthly follow-up visits. The follow-up visits will be scheduled every 30 ± 3 days. If a patient does not complete a follow-up visit within the scheduled period for any reason, we will not collect follow-up data for that time period, and the data for that visit will be considered missing. Patients who fail to attend three consecutive follow-up visits within the scheduled time frame will be excluded from the study. At the baseline visit, we will collect information about demographics, comorbidities, medication history, anthropometric measurements (blood pressure, heart rate, height, and weight), and QoL and hypertensive symptom scales. At each follow-up visit, we will record blood pressure, heart rate, new-onset disease or disease progression, treatment and expenses for the month, and AE data. As a basis for patient compliance judgment and subgroup analysis, we will also record the details of HSM, including the actual dosage, frequency, acupoints, and heat-sensitized sensations at each follow-up visit. QoL and hypertensive symptoms will be assessed at the 3- and 6-month follow-ups. The detailed visit schedule is presented in Fig. 2.

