### Sample size estimation

The primary purpose of sample size estimation is to meet the need for statistical power for primary outcome comparison between randomized groups. Based on the results of our previous nonrandomized studies (not yet published) and expert opinion, we assume that the SBP in the HSM group will be on average 5 mmHg lower than that in the control group after 6 months of HSM treatment, with a common standard deviation of 8 mmHg between the groups. With a type I error probability “α” of 0.05 and type II error probability “β” of 0.20 and the allowance of a 20% attrition rate, a minimum of 51 patients in either the randomized HSM or control group is needed, as calculated by the following formula for the superiority design [22]:
$$ N=2\times {\left(\frac{Z_{1-\frac{\alpha }{2}}+{Z}_{1-\beta }}{\upmu_1-{\upmu}_2}\right)}^2\times {s}^2 $$

We ultimately decided to enlarge the total sample size to 400, as a sample of this size can be supported by funding. We administered a small preference survey to 100 patients at the study sites, which showed that the ratio of patients with a preference (a strong willingness to enter the HSM or control group) to those without a preference (accept the randomization) was approximately 6:1. Considering the feasibility of the study and the need for confounder adjustment, we established a sample size for the voluntary randomization group of 40 (20 per group) such that the size of the preference selection (nonrandomized) group would be 240 (120 per group). The remaining 120 patients will be entered into the compulsory randomization group (60 per group). Figure 1 illustrates the sample size scheme for each arm.

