### Statistical analysis

Data analysis of the primary outcome will be based on the full analysis set constructed by the intention-to-treat principle, whereby patients will remain in their original group regardless of contamination. The per-protocol set will also be analyzed by sensitivity analysis for the primary outcome to evaluate whether contamination impacts the direction of the effect. The secondary outcomes will also be compared based on the per-protocol set. The need to impute missing values will be determined by the proportion of and reasons for missing data. If imputation is necessary, appropriate methods, such as the last observation carried forward, “best-worst-case” scenario and multiple imputation regression modeling, will be chosen according to the distribution of the missing values.

Data analysis will be conducted separately for the randomized and nonrandomized groups, and consistency of effect directions between the two sets of analyses will be evaluated. For the randomized groups, repeated-measures analysis of variance will be employed for the continuous variables measured each month; QoL and symptom scale scores will be compared by *t* tests, and categorical variables will be compared by chi-square tests. These analyses will not be adjusted for covariates unless there are factors that are significantly unbalanced at baseline. For nonrandomized groups, we will utilize repeated-measures ANOVA, linear mixed models, and logistic regression models depending on the data distribution; potential confounders will be adjusted for, including age, body mass index (BMI), baseline SBP, duration of hypertension, type of antihypertensive regimen, diabetes, dyslipidemia, smoking, and alcohol consumption. The between-group difference will be measured by the mean differences for continuous outcomes (i.e., changes in SBP, DBP, dosage of antihypertensive drug, QoL, and hypertensive symptom scores) and the risk ratios (RRs) for binary outcomes (i.e., the response to treatment and incidence of new-onset cardiovascular events).

We are also interested in whether there are different blood pressure lowering effects between HSM regimens with different parameters, which will be explored by the following subgroup analyses with prespecified effect directions based on our clinical experience:

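### Six months of observation in 200 moxibustion patients cannot verify long-term safety, and a chi-square test is unreliable for the few cardiovascular events expected (minor correction)

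*Protocol article*

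**What the plan says.** The closing paragraph of the Discussion makes two claims about what the trial will deliver: "The study will have a sufficient sample size to obtain accurate estimates", and "sufficient 6-month follow-up data to verify long-term safety and patient compliance".

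The Methods set the horizon. Under Interventions and cointerventions: "The study treatments will last 6 months for all patients". Under Visit schedule: "Patients will attend a baseline visit and 6 monthly follow-up visits". No observation after the sixth visit is described.

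Sample size estimation gives 60 per group under compulsory randomization, 20 per group under voluntary randomization and 120 per group by preference. The calculation there serves the systolic blood pressure (SBP) comparison only.

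Secondary outcomes lists "Incidence of new-onset cardiovascular events at month 6, including angina, myocardial infarction, and stroke". For the randomized groups, Statistical analysis compares categorical variables by chi-square tests, and it measures between-group differences by "the risk ratios (RRs) for binary outcomes (i.e., the response to treatment and incidence of new-onset cardiovascular events". Randomized and nonrandomized groups are analysed separately. Adverse events are a different item, under Safety outcomes, recorded at each visit.

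**The concern.** Hypertension is a chronic condition, and HSM is intended as daily self-management. A statement that 6 months of data will verify long-term safety promises something that the design does not observe. The sentence after it looks ahead to wide use in primary care if HSM is shown to be safe and cost-effective, so the safety wording should not exceed the data.

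A smaller matter sits beside it. Cardiovascular events are likely to be few in 80 v 80 patients over half a year. A chi-square test on such a table can give a p-value well away from the exact one, on either side of 0.05 at counts that could occur.

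**Working it through.** **The plan's own figure.** With a difference of 5 mmHg, SD 8, two-sided alpha 0.05 and power 0.80, N = 2 × ((1.960 + 0.842)/5)² × 64 = 40.19 per group. Allowing for 20% attrition, 40.19/0.8 = 50.2, rounded up to 51. The stated 51 reproduces. It concerns SBP only, and no precision target is stated for harms.

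**Exposure to HSM.** Randomized: 60 + 20 = 80. All: 80 + 120 = 200. Each patient is followed for 6 months.

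**What zero occurrences of a harm would exclude.** The exact one-sided 95% upper limit is 1 − 0.05^(1/n).

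| HSM patients | n | Upper limit on 6-month risk |
|---|---|---|
| All | 200 | 1.5% |
| All, after 20% attrition | 160 | 1.9% |
| Randomized | 80 | 3.7% |
| Randomized, after 20% attrition | 64 | 4.6% |

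The chance of seeing at least one case of a 1-in-1000 harm is 1 − 0.999^n: 8% for n = 80 and 18% for n = 200. None of these figures says anything about risk after month 6.

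**Cardiovascular events, randomized set.** The documents give no rate, so an annual rate r is assumed, equal in both arms. Expected total = 160 × 0.5 × r. The Poisson mean per arm is m = 80 × 0.5 × r, and P(at least one arm without events) = 1 − (1 − e^(−m))².

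| Assumed r per year | Expected total | m per arm | P(at least one zero-event arm) |
|---|---|---|---|
| 1% | 0.8 | 0.4 | 89% |
| 2% | 1.6 | 0.8 | 70% |
| 3% | 2.4 | 1.2 | 51% |
| 4% | 3.2 | 1.6 | 36% |
| 5% | 4.0 | 2.0 | 25% |
| 10% | 8.0 | 4.0 | 4% |

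**The chi-square test on a sparse table.** Take 5/80 v 0/80. The expected event count is 5/2 = 2.5 per arm.

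- Pearson, uncorrected: 160 × (5 × 80 − 0 × 75)² / (80 × 80 × 5 × 155) = 5.16, p = 0.023.
- Pearson with continuity correction: 160 × (400 − 80)² / 4,960,000 = 3.30, p = 0.069.
- Fisher, two-sided: 2 × C(80,5)/C(160,5), p = 0.059.

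The article does not say which chi-square version is meant. The uncorrected test falls below 0.05 and the other two do not.

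**The case against.** The strongest reply is that the fault lies in one Discussion phrase. No hypothesis, endpoint, analysis set or decision rule depends on it, and the planned recording of adverse events at each visit, with causality assessment, is something the trial can deliver. That stands, and it limits the weight of the point. *Long-term* is also undefined in the article. But on no reading does the design look past the last treatment month, and the limitations paragraph does not mention the safety horizon.

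Four stronger readings are tempting, and the documents do not support them.

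- A reader might infer that an empty cardiovascular table will be presented as proof of safety. No section says so. Cardiovascular events are listed apart from the safety outcomes, and the sentence on wide use is conditional.
- A reader might infer that the risk ratio will usually be zero or undefined. That depends on the assumed rate: the chance of a zero-event arm drops below one half just above 3% per year. Eligibility extends to age 80 and the outcome includes self-reported angina, so 3% cannot be treated as a ceiling.
- A reader might call low power for these events a fault. The sample size is tied openly to SBP, and no power is claimed for this secondary outcome.
- A reader might reject the compliance half of the sentence too. HSM compliance is assessed at each visit, so that half stands if it means 6-month compliance.

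Handling of sparse tables is often left to an analysis plan, and one may exist. The point here is only that the article names the chi-square test without exception for the randomized groups' categorical variables.

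**Conclusion.** The point holds as a minor correction. The trial can describe 6-month on-treatment safety in up to 200 HSM patients. With no occurrence of a harm it would exclude 6-month risks above about 1.5% (3.7% in the randomized 80). It cannot verify long-term safety. These bounds need no outside figure; they assume that every planned patient is observed, and attrition widens them.

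The cardiovascular part rests on an assumed event rate. At 1% to 3% per year the counts are too small for the chi-square approximation to be trusted. At higher rates a zero-event arm becomes less common, but the expected total is still only 4 at 5% per year. The risk ratio need not be forbidden where it can be estimated. The SBP sample size and primary analysis are not touched.

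**What to change.** In the Discussion, replace the long-term safety claim with 6-month on-treatment safety and add that zero occurrences of a harm in 200 HSM patients would exclude 6-month risks above about 1.5% (3.7% in the randomized 80). Say that the compliance claim also refers to 6 months.

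In Statistical analysis, state that new-onset cardiovascular events will be reported descriptively, as counts per arm with exact confidence intervals, separately for the randomized and nonrandomized sets. State also that any comparison in the randomized set will use an exact method rather than the chi-square test, with a risk ratio shown only where it is estimable.

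The cost is wording and a more modest stated conclusion. No new data, visits or patients are needed.

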## Trial status

The protocol version is 1.1, developed on March 1, 2021, and updated on January 17, 2022. The trial began recruiting on 10 March 2021 and is anticipated to finish in June 2022.

## Data Availability

The datasets collected during the current study are available from the corresponding author on reasonable request.

## Abbreviations

AE: Adverse event
BMI: Body mass index
DBP: Diastolic blood pressure
EQ-5D-5L: Euro-QoL-5 Dimensions-5 Levels questionnaire
HSM: Heat-sensitive moxibustion
QoL: Quality of life
RCT: Randomized controlled trial
SBP: Systolic blood pressure
